### Data management and statistical analyses

Data will be recorded in an electronic database. Unique numeric identifiers will be assigned to all patients, and only this unique number will be included in the study database. Patients’ identification will be solely used for follow-up purposes. The investigators will ensure safekeeping of the patients’ data. Follow-up will be conducted through consultation of medical records and phone contact by trained investigators with large experience in completing participant follow-ups.

Primary and secondary endpoints will be analyzed according to intention-to-treat principles. Patient subgroups such as those presenting with a completely occluded artery, anterior STEMI and pain lasting longer than 3 hours will also be analyzed.

Statistical analyses will be performed using SPSS software. The chi-square test will be used to compare categorical variables, expressed as percentages. Continuous variables, expressed as means ± standard deviation, will be compared using the Student’s *t* test for those with a normal distribution, or the Mann-Whitney test for non-normally distributed data.

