### Sample size

Sample size for the survival analysis was computed with the aid of IBM SPSS Sample-Power software with two-tailed type I error rate set at 0.05 and power at 0.80, conservatively admitting 5 % drop-outs during the RIC protocol and 5 % losses to follow-up. Considering an accrual period of 36 months, a minimum follow-up period of 12 months (maximum follow-up of 48 months), overall primary combined endpoint incidence of 14 % (data from our institution) and a treatment effect of 40 % (arbitrarily set as clinically relevant), we estimate we will need to enroll 224 patients per group (total of 448). Nevertheless, since 8 % of initially enrolled patients (data from our institution) will have unconfirmed STEMI, we will need to enroll 22 more patients per group (246) for a total of 492 patients.

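### The stated comparisons are unadjusted although two recorded baseline factors could be used: a modest loss of efficiency, not a bias

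*Protocol article*

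**What the plan says.** Under Data management and statistical analyses, the article assigns tests by type of variable. For categorical outcomes: "The chi-square test will be used to compare categorical variables, expressed as percentages". Continuous outcomes go to Student's t test or, if not normally distributed, the Mann-Whitney test. None of these adjusts for a covariate.

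The same section uses baseline characteristics in one way only: "Patient subgroups such as those presenting with a completely occluded artery, anterior STEMI and pain lasting longer than 3 hours will also be analyzed".

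Randomization and interventions describes 1:1 allocation in blocks of four and names no stratification factor. Setting and participants makes ST elevation in specified leads (or new left bundle branch block) and symptom onset within 12 h part of eligibility. The data behind both factors therefore exist before allocation.

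The Sample size section presupposes a time-to-event comparison: "Sample size for the survival analysis was computed with the aid of IBM SPSS Sample-Power software". The analysis section names no such method.

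**The concern.** Anterior location and duration of ischaemia may well be prognostic for cardiac death and heart failure; the article's own choice of subgroups suggests its authors think they matter. If they are, an analysis that ignores them discards information already collected. Neither the described allocation nor the stated tests make use of it.

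Three things are at stake:
- power for the primary endpoint, in a single-centre trial that rests on roughly 120 events;
- precision for troponin AUC and LV function;
- an estimate left uncorrected if infarct location happens to differ between arms.

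Timing matters too. The trial is open-label and still recruiting. Covariates named before outcomes are examined by arm are credible; covariates chosen afterwards are not.

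**Working it through.** **1. Reproduce the stated size.** Inputs from the Sample size section: "two-tailed type I error rate set at 0.05 and power at 0.80"; 36 months of accrual with 12 to 48 months of follow-up; 5% drop-outs plus 5% losses; a 40% effect, taken as HR 0.6; and "overall primary combined endpoint incidence of 14 % (data from our institution". No time point is given for the 14%. I read it as the 12-month incidence across both arms, with exponential survival and uniform entry.

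- Events, Schoenfeld: 4 × (1.960 + 0.842)² / (ln 0.6)² = 4 × 7.849 / 0.2609 = 120.3, so 121. Freedman: (1.6/0.4)² × 7.849 = 125.6, so 126.
- Control hazard λ per month: 0.5(1 − e^(−12λ)) + 0.5(1 − e^(−7.2λ)) = 0.14 gives λ ≈ 0.0158.
- Event probability averaged over follow-up, 1 − (e^(−12λ) − e^(−48λ))/(36λ): 0.369 in controls and 0.244 with RIC (using 0.6λ), mean 0.306.
- Per arm: 121/(2 × 0.306) = 198 or 126/(2 × 0.306) = 206. Dividing by 0.90 gives 220 or 229, against the stated 224.

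The plan's figure reproduces within 3%, without any covariate adjustment.

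**2. Power with and without adjustment.** I used 224 × 0.90 ≈ 202 evaluable patients per arm (404), blocks of four, and 3,000 simulated trials per row. Assumed, because the article gives no values: 45% anterior, 50% with pain over 3 h, independent of each other, with the hazard ratios shown. Treatment HR is 0.6 within covariate strata. The base hazard is reset in each row so that overall 12-month incidence stays at 14%.

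| Covariate HRs (anterior, pain) | Unadjusted Cox | Adjusted Cox | Chi-square | Gain, adjusted over unadjusted Cox |
|---|---|---|---|---|
| 1, 1 | 79.3% | 79.3% | 77.4% | 0.0 |
| 1.5, 1.5 | 78.9% | 79.5% | 77.3% | 0.6 |
| 2, 1.5 | 78.0% | 79.7% | 75.3% | 1.7 |
| 2, 2 | 75.7% | 79.2% | 73.5% | 3.5 |
| 3, 2 | 73.0% | 79.2% | 70.9% | 6.2 |

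Each power has a simulation error of about √(0.79 × 0.21/3000) = 0.7 points. Within a row all methods use the same simulated trials. Chi-square trails unadjusted Cox by 1.6 to 2.7 points; that part comes from ignoring time to event, not from lack of adjustment.

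**3. Type I error.** With treatment HR 1 in the same scenarios, the unadjusted analyses (Cox and chi-square) reject in 4.4 to 5.6% of trials.

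**4. Sensitivity to the 14%.** If 14% is reached only by 27 months (about 61 events), the gains in the five rows are −0.1, 1.0, 1.5, 2.5 and 1.9 points. That reading does not reproduce 224. Unadjusted Cox type I error is then 4.4 to 5.7%; chi-square, on about 75 events, gives 5.2 to 6.2%.

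**5. Chance imbalance.** The SD of the between-arm difference in a 45% factor is √(2 × 0.45 × 0.55/n): 5.0 points at n = 202, 4.7 at 224 and 4.5 at 246. A difference above 10 points has probability 4.3%, 3.3% and 2.6% respectively. A 50% versus 40% split would move the unadjusted hazard ratio by roughly (1 + 0.50)/(1 + 0.40) = 1.07 if anterior location carries HR 2, or (1 + 0.50 × 2)/(1 + 0.40 × 2) = 1.11 if it carries HR 3.

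**6. Continuous outcomes.** Covariates explaining a share R² of the variance are worth 1/(1 − R²) times the patients: 1.18 at R² = 0.15 and 1.33 at 0.25. Both R² values are assumptions.

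**The case against.** **The full analysis plan may already adjust.** Only an article is at hand, and covariate models are commonly left to the full protocol or SAP. This stands as a limit. The article neither plans nor rules out adjustment, so the point concerns the comparisons it states. A reader might infer that no adjusted analysis is planned anywhere; the document does not support that.

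**An unadjusted randomised comparison is valid.** This stands. A reader might take chance imbalance in infarct location as bias. It is not: the test already allows for it, and unadjusted type I error stays near 5%. What is lost is efficiency.

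**The trial is not shown to be underpowered.** A reader might infer that power is already below 80%, which would make adjustment a rescue. That requires assigning the 14% to controls at 12 months, when 266 to 276 per arm would be needed. The article calls the 14% an overall figure, and 224 reproduces on an overall 12-month reading.

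**The gain is small and assumption-driven.** For moderate covariates it is 2 points or less, and the article gives no prognostic strengths or prevalences. This stands, and it sets the weight of the point.

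**Adjustment changes the estimand.** The hazard ratio is non-collapsible, so an adjusted one is conditional on the covariates, whereas the planning effect is stated without them: "a treatment effect of 40 % (arbitrarily set as clinically relevant". This stands as a small cost, met by labelling the effect.

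**Conclusion.** The point holds as a recommendation to improve efficiency, not as an error in the plan. The stated tests are unadjusted, no stratification factor is named, and two candidate covariates are recorded and can be fixed before allocation. Adjusted Cox keeps power at 79.2 to 79.7% in every scenario on the reading that reproduces the sample size, while unadjusted Cox falls from 79.3% to 73.0% as the covariates become stronger. The gain is thus about 0 to 2 points for moderately prognostic covariates and 3 to 6 for strong ones, with essentially no loss if they are not prognostic.

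This rests on assumed covariate hazard ratios of 1 to 3, prevalences of 45 to 50%, 14% read as the overall 12-month incidence, and HR 0.6 within covariate strata. The gain for troponin AUC and LV function rests wholly on an assumed R².

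**What to change.** Pre-specify the following before any outcome is examined by arm:

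- **Primary endpoint:** a Cox model with treatment, anterior location (yes/no, from the qualifying ECG) and symptom duration (over 3 h, yes/no, as in the subgroup definition). This also supplies the time-to-event method that the sample size presupposes.
- **Troponin AUC and LV function:** linear regression of log troponin AUC and of LV function on treatment and the same two covariates.
- **Definitions:** measure symptom duration to a time point before allocation, such as presentation. State how patients who qualify by left bundle branch block are coded for location.
- **Coronary occlusion:** do not adjust for it. It is read at angiography, after randomisation.
- **Reporting:** label the adjusted hazard ratio as a conditional effect and give unadjusted results as supportive.

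The cost is a few sentences in the analysis plan and no new data. The one trade-off is that the primary hazard ratio becomes conditional on the two covariates.

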### Ethics

This study is being conducted in accordance with the Declaration of Helsinki 1964 as revised in 2013 and the International Conference of Harmonisation Guidelines for Good Clinical Practice.

Considering that STEMI is a medical emergency, little time is available. Eligible patients are orally informed and asked to participate in the study. Enrollment will be based on witnessed oral consent, and full written informed consent will be obtained by one of the investigators only after the acute phase has been addressed. Patients are notified at enrollment of their freedom to abandon the study at any time without consequences.

The study protocol (version HB-CARD-01; 20/11/2012) has been reviewed and approved by our Institution’s Ethical Committee (“Comissão de Ética para a Saúde do Hospital de Braga”), as verified with the board approval number 94/2012 (submitted and approved).

### Dissemination of results

The trial protocol and results will be published in peer-reviewed journals. The results of the trial will be reported in accordance with the CONSORT (Consolidated Standards of Reporting Trials) statement and its extension to non-pharmacological interventions [17, 18].

## Discussion

Despite its decline in recent years, STEMI mortality in European countries remains high, reaching at least 12 % at 6 months [3, 4]. Current mortality rates can hardly be further improved by PCI developments, strongly suggesting an important role of IRI, which can contribute to up to 40 to 50 % of the final infarct size and is, therefore, a main determinant of HF development [2, 5, 7, 15].

RIC is a safe noninvasive low cost intervention that has shown positive results in mitigating IRI in several clinical settings, including STEMI [12, 13]. So far, only one study evaluated the long-term prognosis of STEMI patients submitted to RIC [14]. However, this study was not initially powered to show an effect on hard clinical endpoints. As such, for the time being, although promising, RIC cannot be advised in evidence-based practice.

RIC-STEMI was designed to evaluate the impact of RIC as adjunctive to PCI in STEMI patients in the combined clinical outcome of cardiac-caused death or hospitalization for HF. Enrollment of the patients began in March 2013, and 324 patients were randomized in just under two years. Considering the number of patients usually referred to our institution, we expect to complete enrollment within 3 years.

## Trial status

RIC-STEMI is still recruiting participants.

From 11 March 2013 to 31 December 2014, 324 patients were enrolled and randomized for RIC-STEMI, but 29 of those were excluded from further analysis because STEMI was not confirmed on coronarography.

RIC was well tolerated by an overwhelming majority of patients.

## Abbreviations

STEMI: ST-elevation myocardial infarction
IRI: ischemia-reperfusion injury
PCI: percutaneous coronary intervention
IC: ischemic conditioning
RIC: remote ischemic conditioning
HF: heart failure
MACE: major adverse cardiovascular events
CABG: coronary artery bypass grafting
MI: myocardial infarction
